### Secondary endpoint analysis

For the secondary endpoint measurements of pathologist and AI-performance, sensitivity and negative predictive values (NPV) are presented as point estimates. Results of the questionnaire on the SN-workflow of Dutch pathology laboratories were summarized by frequencies and percentages. Results of the questionnaire among participating pathologists were averaged and presented per question.

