### **Proposed clinical workflow (see figure below)**

Pathologists in the control arm will perform assessment according to the current clinical workflow. Pathologists in the AI-intervention arm will assess the HE-specimens digitally after the algorithm has assessed these. The output of the algorithm will be available to the pathologist when they assess the H&E specimen. Like in the control arm, if no metastases or tumors are detected on the H&E slide with AI assistance, additional IHC stainings are being performed in all cases, to ensure no metastases or tumors are being missed.

Therefore, the only direct benefit from the algorithm, in this first clinical introduction of AI tumor detection, will be the confirmation of metastases or tumor by the AI-assisted pathologist, in cases for which the non-AI-assisted pathologist would need IHC.

In a second phase, as the reference standard (IHC) will have been determined in all cases for which the AI-assisted pathologist concluded that no tumor or metastases were morphologically visible, we will be analyzing the safety of omitting IHC in these cases.

[figure not shown]

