#### 3.4 Sample size calculation

All SN-specimens assessed within the UMC Utrecht for three consecutive months (August 1st – November 1st 2021) were analyzed. In total, 83 SN-specimens were assessed, for which in 68 cases (81.9%) IHC was performed.

In 24/83 SN-specimens metastases were detected (8 macro-metastases, 8 micro-metastases, and 8 x isolated tumor cells).

- o All 8 macro-metastases were detected without IHC
- o 2/8 micro-metastases were detected without IHC
- o None of the 8 cases with isolated tumor cells were detected without IHC

We presume that the AI-algorithm will detect all metastases for which currently IHC is used. This means that for 14 metastases (6 micro-metastases + 8 ITC) no IHC will be used in the intervention group, whereas in the control group, IHC would be used. This leads to the following proportions per arm:

- $P1 = 68/83 = 0.819$
- $P2 = (68-14)/83 = 0.651$

A one-sided test was used, as we are only interested in a one-sided outcome, i.e. less IHC being performed in the AI-assisted arm. In addition, it is not likely that more IHC will be performed in the AI-assisted arm, as in both arms pathologists make the call whether to perform IHC. So even if the AI-algorithm would not recognize any metastases, the

pathologist would still look at the HE-slide and check whether there are no metastases (morphologically), which is exactly what the pathologists in the other arm are doing.

Calculations were performed in R by using the `power.prop.test` command (see below).

```
> power.prop.test(n=NULL, p1=0.819277108, p2=0.650602409, sig.level=0.05, power=0.8, alternative = "one.sided")

Two-sample comparison of proportions power calculation

      n = 83.61041
     p1 = 0.8192771
     p2 = 0.6506024
sig.level = 0.05
  power = 0.8
alternative = one.sided

NOTE: n is number in "each" group
```

We decided to be conservative and include 90 SN-specimens (i.e. from 90 patients) per arm. This will take approximately 7 to 8 months.

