##### 2. Pathologist performance

- Sensitivity and negative predictive value of the pathologists on the HE-slides, stratified for type of metastases (isolated tumor cells, micro metastases, macro metastases).
- AI-user experience (questionnaire).

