### 6.3 Other study parameters

Number of IHC's that would not have needed to be performed after AI-implementation

In the AI-arm, the number of IHC-stainings which, based on the evaluation of the AI-assisted pathologist, could have been omitted will be determined (i.e. the sensitivity of the AI-assisted pathologist will be determined).

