### Primary endpoint analysis

For the analysis of the primary endpoint, the proportions of IHC-use in all cases of detected SN-metastases were compared, and adjusted risks were calculated using a log-binomial regression model (1-6), with starting values provided by the simple approach suggested by Schwendinger *et al* (7, 8) and 95% confidence intervals (CI) calculated by bootstrapping (n=1,000) (1).

Potential confounders were identified a-priori during discussions with all participating pathologists. Two factors may play a role here. First how diligently a pathologist looks at the HE-section could potentially be influenced by tumor characteristics on biopsy. However, all participating pathologists stated that they virtually always look at an SN without prior looking at any of the tumor characteristics on biopsy. In this light, it is also important to mention that the SN-specimen is always assessed a day before the resection specimen of the tumor itself. Hence, many (if not all) tumor characteristics (either derived from the biopsy or the resection specimen) are unknown to the pathologist who assesses the SN-specimen. Second, some tumor characteristics may influence the visibility of metastasized cells. Two of these potential confounding factors were identified. First, the size of metastases (i.e. macro-metastases ( $\geq 2\text{mm}$ ), micro-metastases ( $< 2\text{mm}$ ) or ITC) influences their visibility to a pathologist (either with or without AI-assistance), and consequently influences the use of IHC. The same holds true for histologic subtype, as for example lobular cancer cells are known to be more difficult to identify on the HE-section.

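### Sensitivity and NPV are planned without confidence intervals, although the per-type groups will be small, and protocol 6.3 equates the number of omittable IHC stains with sensitivity

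*Combined protocol and SAP*

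**What the plan says.** Under Secondary endpoint analysis, the SAP states for pathologist and AI performance that "sensitivity and negative predictive values (NPV) are presented as point estimates". It does not say that intervals are excluded, but none is given for these measures in either document, nor is a threshold or a sample-size basis. The SAP's Primary endpoint analysis does specify 95% confidence intervals, from 1,000 bootstrap samples.

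Protocol 5.1.2 lists "Sensitivity and negative predictive value of the pathologists on the HE-slides, stratified for type of metastases", the types being isolated tumor cells (ITC), micro-metastases and macro-metastases. Section 5.2 repeats the calculation per type.

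Two places look ahead to leaving IHC out. Under Proposed clinical workflow, the protocol says of specimens in which the AI-assisted pathologist saw no tumor that "we will be analyzing the safety of omitting IHC in these cases", with IHC as the reference standard. Section 6.3 says that the number of stains in the AI arm that could have been omitted will be determined, and explains this in parentheses: "i.e. the sensitivity of the AI-assisted pathologist will be determined".

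**The concern.** There are two linked problems.

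First, the trial is sized for the proportion of specimens with IHC, not for accuracy. Split by type of metastasis, each arm has few cases, and a bare percentage does not show how little it establishes. An unqualified 100% for ITC or micro-metastases would look settled when it is not.

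Second, the parenthesis in 6.3 joins two quantities with different denominators. The number of omittable stains comes from the negative reads. Sensitivity is a proportion of the specimens with metastases. Neither gives the risk of omission, which is the share of AI-assisted negative reads in which a metastasis was missed (the false-omission rate, 1 - NPV).

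At stake is how far the results can inform a later decision on omitting IHC, which is the question the protocol sets for its second phase.

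**Working it through.** **Plan's own figure.** The only calculated sample size is for IHC use: p1 = 68/83 = 0.819, p2 = 54/83 = 0.651, one-sided alpha 0.05, power 80%.

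n = [1.645 × √(2 × 0.735 × 0.265) + 0.842 × √(0.819 × 0.181 + 0.651 × 0.349)]² / (0.819 - 0.651)² = 83.61 per arm with unrounded proportions.

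This matches the protocol's R output; 90 per arm are planned. No such calculation exists for sensitivity or NPV.

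**Projected group sizes.** Protocol 3.4 gives a pilot of 83 specimens: 24 with metastases (8 macro, 8 micro, 8 ITC) and 83 - 24 = 59 without. The SAP presumes a similar distribution during the trial. At 90 per arm:
- per type: 90 × 8/83 = 8.7, about 9
- all metastases: 90 × 24/83 = 26.0
- no metastases: 90 × 59/83 = 64.0

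**Exact (Clopper-Pearson) two-sided 95% intervals.** The lower limit is the 2.5% point of Beta(x, n - x + 1) and the upper limit is the 97.5% point of Beta(x + 1, n - x). With no misses the lower limit reduces to 0.025^(1/n). For 9/9 this is 0.025^(1/9) = 0.664. For 64/64 it is 0.025^(1/64) = 0.944, so the false-omission rate can be as high as 1 - 0.944 = 5.6%.

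The outcomes below are illustrations, not predictions.

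| Measure | Outcome | Estimate | 95% CI |
|---|---|---|---|
| Sensitivity, one type | 9/9 | 100% | 66-100% |
| Sensitivity, one type | 8/9 | 89% | 52-99.7% |
| Sensitivity, one type | 7/9 | 78% | 40-97% |
| Sensitivity, all types | 26/26 | 100% | 87-100% |
| Standalone AI, one type, both arms | 17/17 | 100% | 80-100% |
| False-omission rate | 0/64 | 0% | 0-5.6% |
| False-omission rate | 3/67 | 4.5% | 0.9-12.5% |

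A reader with a true sensitivity of 80% for one type would still score 9/9 with probability 0.8^9 = 13%; at 90% it is 0.9^9 = 39%.

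**Sensitivity against omittable stains.** Suppose that no metastasis-free specimen is called positive on H&E, and count negative reads (the documents do not give the number of stains per specimen).
- All 26 metastases found: sensitivity 100%, 64 negative reads, false-omission rate 0/64.
- Three ITC missed: sensitivity 23/26 = 88.5%, 64 + 3 = 67 negative reads, false-omission rate 3/67 = 4.5%.

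The number of omittable stains rises as sensitivity falls, so one cannot stand for the other.

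**Pilot figures.** Without AI, 8 + 2 + 0 = 10 of 24 metastases were found without IHC, a sensitivity of 42%. NPV is 54/68 = 79% if only specimens with IHC count (68 - 14 = 54 negative). It is 59/73 = 81% if every specimen without a metastasis found on H&E counts (83 - 10 = 73). The gap arises because 83 - 68 = 15 specimens had no IHC but only 10 had metastases found without it, which leaves 5 with neither. The denominator therefore has to be stated.

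**The case against.** The strongest reply is that the needed measure is already planned. NPV is a listed secondary endpoint, the false-omission rate is simply 1 - NPV, the workflow section already defines the population of AI-assisted negative reads, and 6.3 already undertakes to count the omittable stains. Only a parenthesis under Other study parameters is wrong, and anyone given the counts could compute an interval. All of this stands and limits the point. It does not supply the intervals, and the SAP does not promise the counts.

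Some stronger inferences are tempting, but the documents do not support them:
- *That the plan equates safe omission with sensitivity.* Section 6.3 never mentions safety, and the workflow section names no measure. Using 1 - NPV for the omission question is a statistical judgement, not something the plan contradicts.
- *That the plan would present small groups as proof of safety.* It announces an analysis and states no conclusion or decision rule.
- *That sensitivity is inflated by easily seen macro-metastases.* Sensitivity is planned per type, which guards against this.
- *That patients are exposed.* IHC is planned for every H&E-negative case in both arms.

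The group sizes are also projections from 83 specimens, and the SAP itself calls the similar case mix an assumption.

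**Conclusion.** The point holds in two parts. First, sensitivity and NPV, the trial's planned accuracy measures, have no stated uncertainty, although the per-type groups are likely to be too small for a point estimate to be informative alone: a perfect result in one type leaves a lower limit of about 66%, and a perfect NPV leaves a false-omission rate of up to about 5.6%. Second, the parenthesis in 6.3 identifies a count of omittable stains with sensitivity, which is incorrect.

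The sizes rest on the pilot case mix, on 90 specimens per arm and, for the negative reads, on no false-positive H&E reads. A different mix would change the limits, but groups of this order would still give wide intervals. The issue is worth correcting because the remedy is cheap. It does not affect the primary comparison.

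**What to change.** **SAP, Secondary endpoint analysis.** Report numerators, denominators and exact (Clopper-Pearson) two-sided 95% CIs for sensitivity, overall and per type, and for NPV, overall. Do this for the pathologists by arm, and for standalone AI by arm and combined. NPV should not be split by type, because a specimen without metastases has no type and the split has no natural denominator. State whether negative reads without IHC count.

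**Protocol 6.3.** Replace the parenthesis with the number of AI-assisted negative reads and the false-omission rate (1 - NPV) with its two-sided 95% CI. Give missed macro-metastases, micro-metastases and ITC each over all AI-assisted negative reads. Any statement about omitting IHC should cite that interval.

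**Cost.** A few sentences in two places and no new data. The accuracy figures will look less certain. The SAP is written in the past tense and the SPIRIT-AI checklist says that results have been presented, so in practice this is a change to the reporting.

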### Sample size calculations

Sample size calculations were based on a retrospective analysis of 83 consecutive SN-specimens from a period of three months in the UMC Utrecht. We assumed that the AI-assisted pathologist would detect all metastases without IHC for which currently IHC is needed, which are mainly micro-metastases and ITC (~15%). Of the 83 cases, IHC was used in a total of 68 cases (0.819), mainly consisting of negative cases and 14 cases of ITC and micro-metastases. We assumed that these 14 cases would be detected by the algorithm, without the need for IHC. This resulted in a presumed proportion of IHC-use in the intervention arm of 0.650 (54/83). This sample size calculation is thus built on two assumptions, being a presumed similar overall distribution of negative cases and cases of ITC, micro- and macro metastases during the trial, and a presumed proportion of IHC-use in the intervention arm based on assumptions of the accuracy of the algorithm. Therefore, the sample size calculation is in theory indirect. However, it was deemed the best way calculate clinically applicable sample sizes for this trial.

We used a one-sided significance level of 5%, as it was deemed impossible to use more IHC

after AI-assistance, and a power of 80%, resulting in a sample size of 166 SNs (83 per arm). As there are uncertainties on the assumption of the amount of metastases that the AI-assisted pathologist would detect without IHC, we decided to include 180 SNs (90 per arm) to be on the safe side.

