### 4.4 Summary of known and potential risks and benefits

Potential risks (zero); patients are at no risk to receive an inferior diagnosis, as the pathologists will always be the one making a definitive diagnosis. In case of doubt, IHC will always be performed.

Potential benefits: reduction of means (IHC), thereby reducing costs. Moreover, we envision improved time management, and an improved work flow for pathologists.

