### 6.1 Primary study parameter(s)

As the primary outcome measure is dichotomous, a simple Chi-squared test will be used to test for differences in the proportion of IHC-use in both arms. Furthermore, relative risks (of IHC-use) will be calculated.

For baseline comparisons between both arms, we will use the appropriate measures (parametric or non-parametric) for categorical (Chi-squared test/Fisher's exact) and continuous parameters (T-test, Mann-Whitney U test).

Although we do not expect differences in patient- and tumor characteristics between both groups, we will adjust for them if they are observed. We do not plan to perform the often used logistic regression model, but we will explore alternative models like Poisson regression with robust standard errors or log-binomial regression, as these will provide adjusted relative risks instead of odds ratio's provided by logistic regression.

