#### Statistical software

Data-analysis were performed with IBM SPSS Statistics version 27.0 and RStudio version 4.2.1, with a significance level set at  $p < 0.05$ .

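### The sample size rests on a one-sided 5% test, but the analysis sections never carry that rule forward; read as two-sided, the all-specimen comparison has about 73% power at 90 per arm

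*Combined protocol and SAP*

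**What the plan says.** **Sizing.** Protocol section 3.4: "A one-sided test was used, as we are only interested in a one-sided outcome, i.e. less IHC being performed in the AI-assisted arm". The R call printed there sets a one-sided alternative at 0.05 with 80% power and returns 83.61 per arm. The SAP, under Sample size calculations, agrees: "We used a one-sided significance level of 5%, as it was deemed impossible to use more IHC" once AI is in use, "and a power of 80%, resulting in a sample size of 166 SNs (83 per arm"). The two documents differ in how strongly they defend the direction. The protocol calls more IHC in the AI arm unlikely, while the SAP rules it out.

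**Margin.** Protocol section 3.4: "We decided to be conservative and include 90 SN-specimens (i.e. from 90 patients) per arm". The SAP explains the increase by uncertainty about how many metastases the AI-assisted pathologist will find without IHC.

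**Analysis.** Protocol section 6.1: "As the primary outcome measure is dichotomous, a simple Chi-squared test will be used" to look for differences between arms in the proportion with IHC. The SAP, under Primary endpoint analysis, fits a log-binomial model with "95% confidence intervals (CI) calculated by bootstrapping (n=1,000"). Under Statistical software it describes the analyses as done "with a significance level set at" p < 0.05. None of these three places gives a direction.

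**Population.** Sizing uses all 83 pilot specimens. The endpoint in protocol section 5.1.1 and the SAP's primary comparison concern IHC use among cases with detected metastases.

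**The concern.** A Pearson chi-squared test on a 2x2 table is non-directional. Its 5% level is that of a two-sided z-test, and a conventional 95% interval matches it. A reader who takes the analysis sections at face value will run a two-sided test, whereas the sample size was justified for a one-sided one.

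Two things follow. First, the stated power does not belong to the test as named in section 6.1. Second, a result with one-sided p below 0.05 and two-sided p above 0.05 could be called positive or negative from the same documents. Such results are not far-fetched. With IHC in 74/90 controls and 63/90 AI-arm specimens, the pooled proportion is 137/180 = 0.761 and z = 0.1222 / √(0.761 × 0.239 × 2/90) = 1.92. That is p = 0.027 one-sided and p = 0.054 two-sided.

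**Working it through.** **Inputs (protocol section 3.4).** p1 = 68/83 = 0.8193; p2 = (68 − 14)/83 = 0.6506; difference d = 0.1687; mean p̄ = 0.7349. These are taken as stated.

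**Formula (as in power.prop.test).** Let A = √(2p̄(1 − p̄)) = √0.3896 = 0.6242 and B = √(p1(1 − p1) + p2(1 − p2)) = √0.3754 = 0.6127. Then n per arm = ((z_α·A + 0.8416·B)/d)², and power = Φ((d√n − z_α·A)/B).

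**Step 1: reproduce the plan.** One-sided, z_α = 1.6449: n = ((1.0267 + 0.5156)/0.1687)² = 83.6. The protocol's figure is reproduced.

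**Step 2: same inputs, two-sided.** z_α = 1.9600: n = ((1.2234 + 0.5156)/0.1687)² = 106.3, so 107 per arm.

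**Step 3: power at 90 per arm.** d√90 = 1.6002.
- One-sided: Φ((1.6002 − 1.0267)/0.6127) = Φ(0.936) = 82.5%.
- Two-sided: Φ((1.6002 − 1.2234)/0.6127) = Φ(0.615) = 73.1%.

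Exact binomial enumeration of the Pearson test agrees: 82.9% and 73.5%.

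**Step 4: is 90 a margin for imperfect detection?** Put p2 = (68 − k)/83, where k of the 14 metastases no longer need IHC. All specimens, 90 per arm:

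| k of 14 | p2 | one-sided | two-sided |
|---|---|---|---|
| 14 | 0.651 | 82.5% | 73.1% |
| 13 | 0.663 | 77.8% | 67.2% |
| 12 | 0.675 | 72.4% | 60.8% |
| 10 | 0.699 | 59.8% | 47.2% |

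One metastasis still needing IHC takes even the one-sided power below 80%.

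**Step 5: the SAP's primary population.** Assume the pilot metastasis rate holds: 90 × 24/83 = 26 metastatic cases per arm. Control proportion 14/24 = 0.583; AI-arm proportion (14 − k)/24. Exact two-sided power of an unadjusted Pearson test:

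| k of 14 | AI-arm proportion | two-sided power |
|---|---|---|
| 14 | 0 | above 99% |
| 12 | 0.083 | 99% |
| 10 | 0.167 | 91% |
| 8 | 0.250 | 70% |

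Sidedness makes little difference here unless detection is well short of the plan's assumption. At k = 8 the normal approximation gives 80% one-sided and 69% two-sided.

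**The case against.** The strongest reply is that neither document declares a two-sided test. Protocol section 3.4 says a one-sided test was used, the SAP repeats the one-sided level, and an undirected p < 0.05 is compatible with both. A one-degree-of-freedom chi-squared statistic is the square of z, so a directional p-value is available. The 95% intervals belong to the log-binomial model, not to the chi-squared test. On that reading, 90 per arm delivers 82.5% and there is no shortfall. This stands in part: the defect is a rule left out of the analysis text, and 73% is conditional on the conventional reading of the named test.

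A reader might also infer that the primary analysis is underpowered. The documents do not support that. The SAP compares metastatic cases only, and power there is high on either sidedness under the plan's own assumptions.

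A reader might further infer from protocol section 4.4 ("In case of doubt, IHC will always be performed") that AI output will create doubt and so raise IHC use. The documents give no figure or statement for that mechanism, and the point does not depend on it. It is enough that the protocol itself claims only that more IHC is unlikely.

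Finally, the SAP is written in the past tense, and its SPIRIT-AI checklist (item 31a) reports conference presentation in 2023. Enrolment cannot change, and a two-sided 5% test does not inflate the type I error. Both points are fair. They limit the remedy to wording but do not remove the ambiguity.

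**Conclusion.** The concern holds as an inconsistency between sizing and analysis. The sample size is explicitly one-sided at 5%, and no analysis section carries that forward. For the all-specimen comparison at the stated 0.819 and 0.651, power at 90 per arm is about 73% if the chi-squared test is read as two-sided. That is about 7 points below the 80% target and 9 below the one-sided 82.5%. The step from 83 to 90 is not a real safety margin for that comparison, because one missed metastasis in 14 uses it up even one-sided.

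It does not follow that the trial as a whole misses its power. The metastatic-case comparison has two-sided power above 99% at 14 of 14 and still 91% at 10 of 14. That rests on 26 metastatic cases per arm at the pilot rate, a control proportion of 14/24, and an unadjusted test in place of the adjusted model.

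**What to change.** 1. In protocol section 6.1 and the SAP's Primary endpoint analysis, state that the primary test is two-sided at 5% with a two-sided 95% confidence interval.
2. Restate power at 90 per arm for that test, labelled by population: about 73% for all specimens at the stated proportions and, separately, the metastatic-case figure with its assumed number of cases and a sensitivity line over the number of metastases spared IHC (for example 14, 12, 10 and 8 of 14).
3. In the SAP, replace the claim that more IHC is impossible with the protocol's weaker statement that it is unlikely.
4. If the sponsor keeps a one-sided test, the analysis section should name a one-sided z-test at 5% and report a one-sided 95% bound with it.

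The cost is wording and a less favourable stated power for the all-specimen comparison. No extra patients are needed.

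### The SAP rounds 83.61 per arm down to 83, and its 90 per arm, chosen as cover for metastases missed on H&E, keeps 80% power on the all-specimen calculation only if none of the 14 is missed

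*Combined protocol and SAP*

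**What the plan says.** Both documents size the trial on IHC use among all sentinel node specimens. The SAP (Sample size calculations) takes the control proportion from the pilot: "IHC was used in a total of 68 cases (0.819". For the AI arm it uses a "presumed proportion of IHC-use in the intervention arm of 0.650 (54/83", which rests on full detection: "We assumed that these 14 cases would be detected by the algorithm, without the need for IHC". Protocol section 3.4 uses the same counts and prints the R result, n = 83.61041 in each group, for one-sided 5% and 80% power. The SAP gives the result as "resulting in a sample size of 166 SNs (83 per arm".

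Both documents then plan 90 per arm. The protocol says "We decided to be conservative and include 90 SN-specimens" and gives no further reason. The SAP does give one. It refers to uncertainty about the number of metastases the AI-assisted pathologist would detect without IHC, and continues "we decided to include 180 SNs (90 per arm) to be on the safe side". Neither document shows power for fewer than 14 found.

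**The concern.** A required sample size is rounded up, so 83 per arm falls short of the stated 80% by the plan's own formula.

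The margin is the more important matter. The SAP names the detection assumption as uncertain and offers the step from 83 to 90 as its answer. A reader will take this to mean that the all-specimen comparison can tolerate some missed metastases at 80% power. The 14 cases are 8 with isolated tumor cells and 6 micro-metastases. In the pilot, pathologists working without AI found none of 8 and 2 of 8 of these types without IHC, so some misses are plausible. If the margin does not cover even one, a non-significant all-specimen result could reflect a few small metastases missed on H&E. It could then be misread as no benefit.

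**Working it through.** **Inputs.** Control IHC proportion p1 = 68/83 = 0.8193. AI-arm proportion p2 = (68 − k)/83, where k is the number of the 14 found without IHC; the plan sets k = 14, so p2 = 54/83 = 0.6506. One-sided 5% (z = 1.6449), 80% power (z = 0.8416), equal arms. All come from protocol 3.4 and the SAP's Sample size calculations.

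**Formulas** (normal approximation, pooled variance under the null, as in `power.prop.test`). Let m = (p1 + p2)/2, d = p1 − p2, s0 = √[2m(1 − m)] and s1 = √[p1(1 − p1) + p2(1 − p2)]. Then

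- n per arm = (1.6449·s0 + 0.8416·s1)² / d²
- power = Φ[(√n·d − 1.6449·s0) / s1]

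**Step 1: reproduce the plan.** For k = 14: m = 0.7349, s0 = 0.6242, s1 = 0.6127, d = 0.1687. This gives n = 83.61, matching the protocol's output. Rounded up it is 84 per arm, or 168 in total. The SAP's rounded proportions (0.819 and 0.650) give 83.37, which also rounds up to 84.

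**Step 2: the rounding.** Power is Φ(0.832) = 79.7% at 83 per arm and Φ(0.848) = 80.2% at 84.

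**Step 3: the margin at 90 per arm.**

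- k = 14: (9.487 × 0.1687 − 1.6449 × 0.6242)/0.6127 = 0.936, so power is 82.5%.
- k = 13: d = 0.1566, s0 = 0.6196, s1 = 0.6096. The argument is 0.766, so power is 77.8%.

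| Found without IHC, of 14 | Power at 90 per arm | n per arm for 80% |
|---|---|---|
| 14 | 82.5% | 84 |
| 13 | 77.8% | 96 |
| 12 | 72.4% | 111 |
| 11 | 66.3% | 130 |
| 10 | 59.8% | 155 |
| 7 | 38.7% | 301 |

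Solving for 80% power at n = 90 gives k = 13.44, so the margin is 14 − 13.44 = 0.56 of one case.

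**Step 4: does the method matter?** The unpooled and arcsine formulas give margins of 0.72 and 0.63 of a case. Exact binomial enumeration of the one-sided test at 90 per arm gives 82.9% for k = 14 and 78.2% for k = 13. All agree that one miss takes power below 80%.

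**Step 5: the comparison among detected metastases.** Protocol 5.1.1 and the SAP's Primary endpoint analysis define the primary comparison as IHC use among detected metastases. Assume pilot rates: 24/83 positive, so 90 × 24/83 = 26.02 positives per arm; control IHC use 14/24 = 0.583; AI-arm IHC use (14 − k)/24. The same power formula, one-sided, gives:

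| Found without IHC, of 14 | Approximate power |
|---|---|
| 13 | 99.9% |
| 10 | 94.7% |
| 8 | 80.1% |
| 7 | 69.1% |

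For k = 8: d = 0.3333, s0 = 0.6972, s1 = 0.6562. The argument is (5.101 × 0.3333 − 1.6449 × 0.6972)/0.6562 = 0.844. With so few positives the approximation is rough.

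**The case against.** Several points on the other side have weight.

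- *The rounding has no consequence.* This stands. It concerns one specimen per arm below a planned 90, and the exact enumeration gives 80.4% even at 83. It is a reporting correction against the plan's own formula.
- *The primary analysis is a different comparison.* This stands and limits the point. A reader might infer from the all-specimen table that the trial is underpowered for its primary endpoint. The documents do not support that: among detected metastases, step 5 shows room for several misses. However, the SAP attaches its 80% and its margin to all specimens, and protocol 6.1 can be read as testing all specimens, so the all-specimen claim still needs correcting.
- *The plan is open about its assumptions.* The SAP names both assumptions and calls the calculation indirect. That discloses the uncertainty. It does not support the further statement that 90 per arm provides for it.
- *Detection may be near complete.* The 99.3% sensitivity in protocol 4.2 would give 0.993 × 14 = 13.9 found, above break-even. It is a vendor figure with no breakdown by metastasis size, so it is weak support for these 14 cases.
- *The control proportion may be higher.* Protocol 3.4 lists 8 + 2 + 0 = 10 metastases found without IHC. If every H&E-negative case is stained, that implies 83 − 10 = 73 stained, not 68. With 73/83 as an assumption, power at 90 per arm is 84.3% with 13 found and 79.6% with 12, so the margin would cover one miss but not two. Both documents calculate with 68/83.

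**Conclusion.** The point holds for the calculation that the SAP presents. The required size is 84 per arm, not 83, which is a trivial error. The step to 90 per arm does not provide the protection the SAP gives as its reason: it covers 0.56 of one case, and a single miss leaves power at 77.8%, about 2 points below 80%. Power falls gradually with further misses. This rests on 68/83, one-sided 5%, equal arms and the pilot case mix.

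Two stronger readings go too far. One is that the whole trial has adequate power only in the best case; the primary comparison among detected metastases tolerates several misses on pilot rates. The other is that the protocol makes the same false claim. Section 3.4 calls 90 conservative, but does not tie that word to missed metastases, and 90 does exceed 83.61.

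**What to change.** In the SAP's Sample size calculations:

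1. Replace 166 specimens (83 per arm) with 168 (84 per arm).
2. Replace the closing safety phrase with the power at 90 per arm, labelled as applying to IHC use among all specimens: 82.5% if 14 are found without IHC, 77.8% if 13, 72.4% if 12, 66.3% if 11, 59.8% if 10 and 38.7% if 7.
3. Next to it, state that the primary comparison is among detected metastases, and give its approximate one-sided power with the assumptions shown (about 26 positives per arm, control IHC use 14/24): 99.9% if 13 are found, 94.7% if 10, 80.1% if 8 and 69.1% if 7. Without this, the all-specimen figures would be taken for the trial's power.

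A null all-specimen result should be read against the first set of figures. No specimens, tests or estimates change. The cost is a few sentences and a less favourable stated margin for the all-specimen comparison.
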